### ONT MinION Nanopore Sequencing

For the direct sequencing protocol, nucleic acid extracts will undergo short multiple-displacement amplification reactions followed by purification and concentration using Monarch PCR and DNA cleanup columns. The nucleic acid extract will be checked for DNA yield using a QBIT 3.0 instrument, followed by a nanopore library preparation using the ONT Rapid Sequencing Kit. The prepared sample will be loaded onto a MinION device using the R9.4.1 flow cell and run for 24 hours. Time-stamped fast5 files will be stored on UQ research data manager (RDM) for emulated real-time analysis. Taeper (https://github.com/mbhall88/taeper) will be used for emulating real-time sequencing for subsequent online analysis. The following computing steps will be carried out as a streaming pipeline based on the real-time data emulation: base-calling will be carried out using Guppy v4.0.11 run on high performance GPU (graphics processing unit) computing facilities at UQ; subsequent quality control with nanoq (https://github.com/esteinig/nanoq); species classification and identification of acquired resistance genes using JAPSA (https://github.com/mdcao/npAnalysis); and strain identification using Sketchy (https://github.com/esteinig/sketchy), for Klebsiella pneumoniae and Staphylococcus aureus identified infections. JAPSA calculates confidence intervals for the proportion of reads generated by each species identified. A species will be classified as identified if the 95% lower confidence interval of the proportion of reads from this species is greater than 0.

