#### Secondary Outcomes

Secondary outcomes are:
1) Diagnostic accuracy of MinION nanopore pathogen sequencing direct from whole blood

2) Time to pathogen identification and susceptibility testing using MinION nanopore pathogen sequencing 

a) direct from whole blood 

b) from positive blood culture broth. 

3) Evaluation of direct MinION nanopore pathogen sequencing predictive capabilities using complete reference genomes from positive blood culture broth.

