### Statistical Methods

The primary outcome measure, time to optimal antimicrobial therapy will be reported by median and interquartile range. Comparison between projected time to optimal antimicrobial therapy using an integrated diagnostic sequencing and dosing algorithm will be compared with the observed time to optimal therapy using a suitable non-parametric test such as the Kruskal-Wallis test. Diagnostic accuracy of MinION nanopore pathogen sequencing will be reported as sensitivity, specificity, positive and negative likelihood ratios against the composite reference standard reported above and illustrated by a 2x2 table. Appropriate methods to handle missing data will be developed following an investigation of the pattern of missingness. Where appropriate, multiple imputation will be used to replace missing values from a distribution of plausible values.

The full protocol, patient-level dataset and statistical code will be made available on reasonable request.

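### The species-calling rule tests the read proportion against zero rather than background, so a constant background becomes more likely to be called as reads accumulate

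*Protocol article*

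**What the plan says.** All of the rule stands in the protocol article, under ONT MinION Nanopore Sequencing. Before sequencing, "nucleic acid extracts will undergo short multiple-displacement amplification reactions". The library is then "loaded onto a MinION device using the R9.4.1 flow cell and run for 24 hours". The stored, time-stamped output is replayed as a stream through base-calling, "subsequent quality control with nanoq", species classification and resistance-gene detection.

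On the call itself the article says that "JAPSA calculates confidence intervals for the proportion of reads generated by each species identified". A species counts as identified "if the 95% lower confidence interval of the proportion of reads from this species is greater than 0". It gives no interval method, expected read total or background read level.

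The call is the index test. Secondary Outcomes lists "Diagnostic accuracy of MinION nanopore pathogen sequencing direct from whole blood" and also time to pathogen identification. Statistical Methods adds: "Diagnostic accuracy of MinION nanopore pathogen sequencing will be reported as sensitivity, specificity, positive and negative likelihood ratios".

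**The concern.** A lower limit above zero rejects the hypothesis that the species contributes no reads at all. In sequencing of amplified extracts from blood that is the wrong null. Reagent or skin DNA and taxonomic misassignment can give a species a small but non-zero share of reads when it is not the pathogen. The relevant question is whether the share exceeds that background.

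Two results are at stake. Specificity and the likelihood ratios fall directly on the positivity rule. Time to pathogen identification may come out too short if a call rests on background reads that arrive before there is real evidence for the organism.

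**Working it through.** The article states no read threshold, so there is no figure to reproduce. The check asks what the rule implies.

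**Inputs.** From the article: a 95% level (sidedness not stated) and a cut-off of 0. Assumed, because the article is silent: interval method (a range of standard ones), total reads n, and background share e of a species that is not the pathogen.

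**Step 1: smallest read count x whose lower limit exceeds 0, per-species intervals.**

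- Wald: x − z√(x(1 − x/n)) > 0, which for x much smaller than n means x > z². Two-sided z² = 1.96² = 3.84, so x = 4. One-sided z² = 1.645² = 2.71, so x = 3.
- Percentile bootstrap: 4 two-sided, 3 one-sided.
- Agresti-Coull: 2.
- Wilson, Clopper-Pearson, Jeffreys: 1. For example, at n = 100,000 and x = 1 the Clopper-Pearson limit is 2.5 × 10⁻⁷ and the Wilson limit 1.8 × 10⁻⁶, both above 0.

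These thresholds were the same at every n tried from 50 to 1,000,000.

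**Step 2: the same, simultaneous intervals across species.**

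- Bonferroni-Wald: 8 reads for 10 species, 13 for 100, 17 for 1,000.
- Sison-Glaz multinomial, 10 minor species beside one dominant class:

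| Total reads | Dominant class 99% | Dominant class 90% |
|---|---|---|
| 100 | not run | 6 |
| 1,000 | 7 | 18 |
| 10,000 | 19 | 55 |
| 100,000 | 57 | 173 |

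**Step 3: chance of calling one background species.** This is P(X ≥ threshold), X binomial(n, e). With e held at 0.01%:

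| Total reads n | Expected background reads | 1-read threshold | 4-read threshold |
|---|---|---|---|
| 1,000 | 0.1 | 9.5% | about 0% |
| 10,000 | 1 | 63% | 1.9% |
| 100,000 | 10 | about 100% | 99.0% |

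With 10 such species, independent, at n = 10,000, the chance of at least one false call is 1 − (1 − 0.632)¹⁰, about 100%, with the 1-read threshold, and 1 − (1 − 0.0190)¹⁰ = 17% with the 4-read threshold.

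**Step 4: does a simultaneous interval remove the problem?** From 10,000 to 100,000 reads the Sison-Glaz threshold rises about threefold (57/19 = 3.0; 173/55 = 3.1), while background reads at a fixed share rise tenfold. The share needed for a call therefore falls: from 0.19% to 0.057%, or from 0.55% to 0.173%.

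- Background 0.1%, dominant class 99%: false call 0.7% at 10,000 reads, about 100% at 100,000.
- Background 1%, dominant class 90%: 1.4% at 1,000 reads, about 100% at 10,000.
- Background 0.1%, dominant class 90%: near 0 at both 10,000 and 100,000 reads.

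The size depends on the scenario; the direction with depth does not.

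**Step 5: testing against background instead.** Requiring the two-sided Wilson lower limit to exceed e means x > ne + 1.96√(ne(1 − e)).

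- n = 10,000, e = 0.1%: 10 + 1.96√9.99 = 16.2, so 17 reads; false call 2.7%.
- n = 100,000, e = 0.1%: 100 + 1.96√99.9 = 119.6, so 120 reads; false call 2.8%.
- About 1 expected background read: 3 reads; false call 8.0%. This is below the 63% of the 1-read rule but above the 1.9% of the 4-read rule.

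The false-call chance no longer climbs with depth. These figures take e as known and constant between runs; variation between runs would raise them.

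**The case against.** Four stronger readings are tempting, and the article supports none of them.

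- **The rule is a one-to-four-read threshold.** That holds only for ordinary per-species intervals. The article names the software but not the interval, and simultaneous intervals give much higher counts.
- **Background reads will become pathogen calls.** Depth and background rate are both absent. At 10,000 reads and a 0.001% background, a 4-read threshold gives a false-call chance of about 0%.
- **The first crossing by any species sets the identification time.** The streaming design makes this possible, but time to identification is not defined that way.
- **The primary outcome is distorted.** Statistical Methods compares projected with observed time without saying how the projection uses the species call, so an effect there is inference.

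It is also fair to say that an article condenses a fuller protocol, where negative controls and handling of contaminants commonly sit. Their absence here is therefore not the finding. That defence does not reach the cut-off itself, which is stated in operative form.

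Finally, this is a pilot, specificity will be reported, and the raw files are kept, so false calls could be seen and the rule changed later. This stands in part: it makes the remedy cheap. But the Introduction puts culture yield below 50% in most ICU studies, so an extra call may be hard to tell from a pathogen that culture missed, and a cut-off chosen after seeing specificity would be tuned to the result.

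**Conclusion.** The concern holds for the zero cut-off as written. Whatever interval the software uses, a lower limit above zero makes no allowance for background, and a constant background share becomes more likely to be called as reads accumulate. That conclusion assumes only that background is not exactly zero.

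The size cannot be fixed from the article. The implied threshold is 1 to 4 reads under ordinary per-species intervals and roughly 6 to 173 under the simultaneous intervals tried. The false-call chance runs from near 0 to near 100% over the assumed depths and backgrounds. The threat to specificity is direct; that identification times may be too short is a possibility, because the timing rule is not given. It is a cheap improvement worth making before accuracy is assessed.

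**What to change.** 1. State the interval method, its sidedness, and whether it is per species or simultaneous.
2. Call a species only if the lower 95% limit exceeds that species' background read proportion. Estimate the background from negative controls if they were run. Otherwise use a robust summary, such as a median or upper quantile, across the other Phase 1 runs. Reads that disagree with culture must not all be treated as background, since some will be true pathogens that culture missed.
3. Freeze the cut-off before Phase 2 data are analysed and apply it unchanged. Trial Status says Phase 2 recruitment began in March 2021, so the freeze has to precede analysis. For Phase 1 accuracy, use a leave-one-out background or label the estimate as derivation, so that the same patients do not both set and test the cut-off.
4. Report sensitivity, specificity and time to identification over a range of cut-offs, including the present zero rule. Stricter values belong in the range: at 2.7% per species, 10 independent background species still give 1 − 0.973¹⁰ = 24% for at least one false call.
5. For time to identification, add a persistence rule usable in real time, for example that the call holds over a fixed number of further reads. Persistence to the end of the 24-hour run would use data that a real-time user does not yet have.

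The work is a re-analysis of the stored time-stamped fast5 files. The price is somewhat lower sensitivity and later identification times than the zero rule gives.

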### Statistical Methods

The primary outcome measure, time to optimal antimicrobial therapy will be reported by median and interquartile range. Comparison between projected time to optimal antimicrobial therapy using an integrated diagnostic sequencing and dosing algorithm will be compared with the observed time to optimal therapy using a suitable non-parametric test such as the Kruskal-Wallis test. Diagnostic accuracy of MinION nanopore pathogen sequencing will be reported as sensitivity, specificity, positive and negative likelihood ratios against the composite reference standard reported above and illustrated by a 2x2 table. Appropriate methods to handle missing data will be developed following an investigation of the pattern of missingness. Where appropriate, multiple imputation will be used to replace missing values from a distribution of plausible values.

The full protocol, patient-level dataset and statistical code will be made available on reasonable request.

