## Objectives

### Primary Objective

To estimate the reduction in time to effective antibiotic therapy in children and adults with sepsis using rapid pathogen sequencing combined with dosing software when compared to conventional diagnostic and therapeutic regimens.

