### Outcomes

#### Primary Outcome

The primary outcome is time to effective antimicrobial therapy defined as trough drug concentrations above the MIC of the pathogen.

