**Figure 1 f1:**
[figure not shown]
Study flow diagram. Phase 1: In an initial observational phase of the study, participants will be recruited to a diagnostic accuracy study of MinION nanopore pathogen sequencing. The sample size for this phase of the study is 50 patients with blood culture-confirmed sepsis admitted to ICU. Phase 2: In Phase 2, consecutive patients with suspected sepsis admitted to ICU will undergo MinION nanopore pathogen sequencing integrated with personalised antibiotic therapy using a combination of Bayesian dosing software (ID-ODS™) and measured antibiotic plasma concentrations. A senior ICU pharmacist/clinician at each site will lead this software-guided intervention of antimicrobial dose optimisation. All dosing regimens will be checked by both the senior ICU pharmacist and attending ICU consultant prior to prescription. The final decision regarding the use of the optimised dosing of antibiotics will remain at the discretion of the attending ICU consultant. Software-guided dosing will continue until either: 1) the study antibiotic(s) have been ceased by the treating clinician, 2) the patient is discharged from ICU, 3) after 5 days of study antibiotic therapy. If antibiotic therapy is still required thereafter, dosing will be guided by the treating clinician. Adherence to dosing strategies informed by the dosing software will be supported by the use of senior ICU pharmacists trained in the use of this software-guided approach to antimicrobial dose optimisation. All dosing regimens will be checked by both the senior ICU pharmacist and attending ICU consultant prior to prescription, to ensure appropriateness and safety.

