### Study Samples

Initial study samples will be obtained during the course of the routine clinical sepsis workup. Samples will be stored until consent to participate has been sought, and will then be analysed if consent is given, or destroyed if consent is not given or revoked.

The following study samples will be obtained: i. A single study sample will be taken into an EDTA container at the time of recruitment to the study, and as close to the time of initial blood culture sampling on suspicion of sepsis. (Time=zero). Routine clinical sampling should include appropriate volumes of blood and other clinical samples for culture and susceptibility testing (**Table 2**).

**Table 2 T2:** Appropriate study sample volumes according to age, and sample type. ‘T’ is time of sampling in hours since recruitment.

Age category	EDTA (T=0)	Plasma (T=24,48,72,96h)
Infants and Young children (<5y)	1-2ml	0.5ml
Older children (5-12y)	2-6ml	1-2ml
Adolescents and adults (>12y)	6-10ml	3-5ml

The volume of blood obtained (for both children and adults) will be documented at the time of recruitment and sampling. Consent will be sought to use residual EDTA samples for the evaluation of emerging, rapid methods of bacterial detection and antimicrobial resistance identification.

ii. Plasma samples will be taken at the following time points of antibiotic therapy: at 24 hours, 48 hours, 72 hours and 96 hours post-commencement of antibiotic treatment to determine if target antibiotic plasma concentrations have been reached.

Clinical samples will be processed in line with existing laboratory requirements. Study EDTA samples will be stored at 4°C before shipping to The University of Queensland Centre for Clinical Research (UQCCR) and the Queensland Paediatric Infectious Disease (QPID) laboratory. Bacterial isolates will be stored at -80°C before shipping to UQCCR. Samples will be de-identified before shipping, and labelled with a study ID. Samples at UQCCR will be stored at -80°C until analysis.

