### Laboratory Methods

Routine clinical samples will be processed in NATA accredited laboratories at Pathology Queensland. Time to blood culture growth, time to pathogen identification, and time to susceptibility testing completion will be collected.

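### The primary comparison sets a projected time under the algorithm against an observed time, although Phase 2 is described as delivering the algorithm and measuring concentrations

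*Protocol article*

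**What the plan says.** All references are to the protocol article.

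- The Objectives section sets this as the primary one: "To estimate the reduction in time to effective antibiotic therapy in children and adults with sepsis using rapid pathogen sequencing combined with dosing software", against conventional diagnosis and treatment.
- Primary Outcome: "time to effective antimicrobial therapy defined as trough drug concentrations above the MIC of the pathogen".
- Statistical Methods: "projected time to optimal antimicrobial therapy using an integrated diagnostic sequencing and dosing algorithm will be compared with the observed time". A Kruskal-Wallis test is given as an example of a suitable test, and the outcome is summarised by median and interquartile range. The section does not say how the projection is built, or which patients or phase supply either time.
- Figure 1 legend, on Phase 2: "consecutive patients with suspected sepsis admitted to ICU will undergo MinION nanopore pathogen sequencing integrated with personalised antibiotic therapy", using dosing software together with measured plasma concentrations. Pharmacist and consultant check each regimen before prescription, and the consultant decides whether to use it. Trial Status calls Phase 2 interventional.
- Study Samples: plasma is drawn at 24, 48, 72 and 96 h of antibiotic therapy, with no restriction to one phase. For the initial samples: "Samples will be stored until consent to participate has been sought, and will then be analysed if consent is given". Samples are then shipped, and at the research centre they are kept at -80°C until analysis.
- ONT MinION Nanopore Sequencing: "Time-stamped fast5 files will be stored on UQ research data manager (RDM) for emulated real-time analysis".
- Laboratory Methods, on the routine laboratory: "Time to blood culture growth, time to pathogen identification, and time to susceptibility testing completion will be collected".

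**The concern.** The primary objective asks how much sooner patients reach an effective concentration under the algorithm. A projected time has to suppose when the sequence result would have been available, that someone would have acted on it, and that the resulting dose would have reached target. These are parts of the effect to be estimated. The observed side contains whatever delay and failure occurred in practice.

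The two sides may also be recorded differently. An observed time can be known only from scheduled samples a day apart, whereas a modelled time can take any value.

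A further difficulty is that the article gives two accounts of sequencing. The Figure 1 legend has Phase 2 patients undergo sequencing integrated with their antibiotic therapy. The nanopore section describes a replay of stored files. If results are not returned to clinicians in real time, a measured Phase 2 effect is an effect of dosing only. If they are returned, times under the whole algorithm can be measured.

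At stake is whether the trial's main result can be read as an effect of the algorithm or only as a model of one.

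**Working it through.** **1. The plan's own figure.** Recruitment is about 150 patients with suspected sepsis in Phase 1, to yield 50 culture-confirmed, plus 50 in Phase 2: 150 + 50 = 200. This agrees with the approximately 200 in the abstract. No alpha, power, effect size or standard deviation is stated, so there is no power calculation to reproduce.

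**2. Is a measured comparison available?** The abstract plans pharmacokinetic samples from the approximately 200 patients, so from both phases. MICs come from broth microdilution of isolates, and severity is among the data collected. Measured times can therefore be obtained in culture-positive patients in both phases. If the Phase 1 yield of 50/150 = 33% also holds in Phase 2, the expected number there is 50 × 50/150 = 16.7, about 17.

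**3. Which observed time is the comparator?** Phase 2 patients receive software-guided dosing, so their observed times do not represent conventional care. The natural conventional comparator is Phase 1, but the article does not say so.

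**4. Effect of the sampling grid.** If observed times are read at the next scheduled sample, each one reached by 96 h moves later by between 0 and 24 h. A continuous projection does not move. For a true median of 36 h (an assumption), the next sample is at 48 h, so the apparent gain is 48 − 36 = 12 h with no effect at all.

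**5. Simulated consequence.** Assumptions, none of them in the article: lognormal true times with median 36 h and log-SD 0.5 or 0.7, no true effect, two independent groups of 50, Kruskal-Wallis test at two-sided 0.05, 3000 runs. The projected time is the true time minus an omitted delay, with a floor of 1 h. In the last column, observed times are rounded up to the next 24 h and capped at 120 h.

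| Omitted delay | Rejections, log-SD 0.5 | Rejections, log-SD 0.7 | Gain in median with 24 h grid |
|---|---|---|---|
| 0 h | 4.3% | 5.1% | about 12 h |
| 6 h | 39.8% | 24.7% | about 18 h |
| 12 h | 90.6% | 70.1% | about 24 h |
| 24 h | 100% | 99.6% | about 36 h |

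The two rejection columns use continuous observed times. With no omitted delay but observed times on the grid, rejections are 86.7% (log-SD 0.5) and 62.3% (log-SD 0.7).

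**6. Precision of the measured contrast.** With 50 versus 17 patients and the same log-SDs, the standard error of the log ratio is SD × √(1/50 + 1/17) = SD × 0.281, that is 0.140 or 0.197. The 95% interval then runs from the estimate divided by, to the estimate multiplied by, exp(1.96 × 0.140) = 1.32 or exp(1.96 × 0.197) = 1.47, before adjustment.

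**The case against.** The strongest reply is that the projection is undefined in a condensed article, and that its rules may stand in the full protocol, which the article offers on request. A reader might infer that the projection leaves out real delays, assumes every recommended dose is accepted and reaches target, and is therefore biased in one direction. The article states none of this. This part of the reply stands, and the bias can only be put conditionally.

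Nor is every delay a fair charge against the algorithm. Holding samples for consent and freezing them are study logistics, and counting them could bias against it. The replay uses time-stamped files, so sequencing run time is kept.

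A reader might also attach a size in hours. If 10% to 30% of patients missed target at first and waited one more 24 h sample, the mean would shift by 0.10 × 24 = 2.4 h to 0.30 × 24 = 7.2 h. Those percentages are assumed, and the plan reports medians, which might hardly move. An assumed total of omitted delay has no anchor in the article either.

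It would also go too far to say that measured Phase 2 times are unused. The median and interquartile range of the primary outcome are not limited to projections, and secondary objective iv compares attained concentrations under software and traditional dosing. What they lack is a place in the stated primary comparison.

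Finally, replacing the projection by a between-phase contrast as the primary analysis is debatable. That contrast is confounded and small. If sequencing is only replayed, it would not address sequencing combined with dosing, for which a projection may be the only estimate available. Comparing projected and observed times in the same conventionally treated patients would avoid between-phase confounding. The study is also a pilot that sets out to estimate, and it openly calls the quantity projected.

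None of this settles which patients supply each time, removes the conflict over sequencing, or turns a modelled time into a measured one.

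**Conclusion.** The concern holds in a limited form. The stated primary comparison uses a modelled time for the algorithm, although measured times under at least its dosing part are collected. The projection will tend to overstate the reduction if it is finer-grained than the observed times or omits transport, preparation, sign-off or non-acceptance. Whether it does, and by how much, cannot be established from the article.

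The 12 h grid effect and the rejection rates illustrate the risk. They rest on assumed distributions and on independent groups of 50, which the article does not specify. The conflict between the Figure 1 legend and the nanopore section needs no assumption and decides what any measured Phase 2 effect means.

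**What to change.** 1. Reconcile the Figure 1 legend, the nanopore sequencing section and Statistical Methods on whether sequence results reach clinicians in Phase 2. State which patients and which phase supply the projected and the observed times.
2. Alongside the projection, report the measured time in Phase 2 against the measured time in Phase 1 among culture-positive patients with a MIC. Give it as an estimate with a confidence interval, adjusted for child or adult and for severity. If sequence results are not returned in real time, call it an effect of dosing only.
3. Label the projected comparison as modelled. Start its clock at blood draw, and include transport, extraction, amplification and library preparation. Show research-only consent hold and frozen storage separately. Read projected and observed times on the same sampling grid, and check the projection against measured Phase 2 times.
4. If projected and observed times come from the same patients, use a paired test, since Kruskal-Wallis treats the groups as independent.

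The cost is mainly analysis wording, since the samples, MICs and clinical data are already planned. Item 3 also needs a recorded or stated duration for each handling step. The downside is that the between-phase contrast is non-randomised, with about 50 versus 17 patients, so it is imprecise and open to confounding. It should be presented as an estimate and not as a test of efficacy.
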